In the intervention arm, assignment to a cohort was done based on GA at the time of the pre-determined cohort start date (i.e., Meeting 1). Eligible women unable to attend the first meeting were not consented or assigned to a group; they were advised to continue with standard individual ANC. If a woman was eligible for the study, but there were no open cohorts (e.g., the appropriate cohort was full), she was advised to continue with standard individual ANC. In the control arm, all eligible women who were willing to participate were consented. Written consents were obtained for all study participants in their language of choice (from the five options). A baseline survey was administered immediately after the consent process.

If it was not possible to recruit a minimum of eight women at least three days before the scheduled cohort start date, the cohort was cancelled, and the assigned women re-evaluated for eligibility into another cohort. Women who become ineligible to participate due to cohort cancellation were advised to continue with standard individual ANC. Their data were then coded to reflect cohort cancellation and retained for reporting purposes. However, they were removed from the study sample, and no additional follow-up was done for these women.

***Sub-national health managers and health facility in-charge.*** Sub-national health managers (i.e., county-level in Kenya; state-level in Nigeria) responsible for overseeing reproductive health programs were recruited by study staff via phone at the end of Phase 1 to participate in the in-depth interviews (IDIs). Priority was given to managers known to have had exposure to G-ANC at the end of Phase 1. An appointment for a face-to-face interview was scheduled with each respondent.

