### Data analysis

Data analysis and the reporting of results for this study will be conducted in accordance with norms for analyzing cluster randomized trials as described in the Consolidated Standards of Reporting Trials guidelines
^53^.

***Quantitative data analysis.*** Descriptive analysis of quantitative variables will be done using measures of central tendency (mean, median), measures of dispersion (range, standard deviation), and proportions (frequencies, percentages) as appropriate. Next, differences between the two study arms will be assessed using chi square test. Potential confounding factors, such as the women’s age will be assessed.

The primary outcome analysis will be done based on the intention-to-treat analysis. Participant’s data will be analyzed based on the groups to which they were randomized to compare the proportions of facility-based deliveries between the two study arms. The endpoints will be analyzed using a generalized estimating equations multivariable logistic regression model. The model will adjust the estimates for imbalances in the baseline characteristics.

Secondary analysis will be conducted to explore the uptake of services offered at ANC and during the 12-month post-delivery period, such as FP and child immunization. All statistical analysis will be performed using the
R statistical software
^54^. Subgroup analysis will be conducted for specific subgroups to determine if there was a differential effect of the interventions. The amount of missing data will be assessed for each variable and overall for the sample. If more than 5% of data are missing, multiple imputation methods will be used, assuming data are missing at random
^55^.

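### Intervention-arm women who cannot be re-placed after a cohort cancellation are removed and not followed, so the primary analysis is not the intention-to-treat analysis stated

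*Protocol article*

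**What the plan says.** In the protocol article, Methods, Recruitment and consent (pregnant women), group-care cohorts have a minimum size. The rule starts "If it was not possible to recruit a minimum of eight women at least three days before the scheduled cohort start date, the cohort was", and its consequence is that the group does not go ahead. Cancellation does not by itself end participation: the article next has "the assigned women re-evaluated for eligibility into another cohort". Only women whom the cancellation leaves ineligible are sent to standard individual antenatal care. Of them it says "Their data were then coded to reflect cohort cancellation and retained for reporting purposes". The sentence after that sets out what happens to their place in the trial: "However, they were removed from the study sample, and no additional follow-up was done for these women".

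The Data analysis section says: "The primary outcome analysis will be done based on the intention-to-treat analysis". It adds that data are analysed by randomised group. It gives no exception for cancelled cohorts and defines no modified analysis set.

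Study design makes the health facility the unit of randomisation, and the abstract places randomisation before enrolment.

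**The concern.** An intention-to-treat comparison keeps everyone who entered the trial in the arm to which her facility was randomised, whether or not the intervention reached her. Here a woman enters at an intervention facility, the group she was promised does not form, and she leaves the data set because it did not form. A similar woman at the matched control facility stays in.

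Two things are at stake. The first is comparability: the intervention arm loses women by a process that cannot operate in the control arm, and that is probably more common where recruitment is slow. The second is meaning: the article wants to inform decisions on whether group care is feasible and more effective than individual care, and a cohort that cannot be filled is part of that answer. Because follow-up stopped, neither the 12-month family planning outcome nor the place of birth was collected for these women. An analysis plan written later cannot repair that from the trial data alone.

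**Working it through.** **1. Were these women in the trial?** No single sentence says that they had consented, but the inference is strong:
- Consent and cohort assignment go together: "Eligible women unable to attend the first meeting were not consented or assigned to a group". The cancellation rule concerns women who had been assigned.
- "A baseline survey was administered immediately after the consent process", so baseline data would exist before a later cancellation.
- Their data were kept, whereas the same section says no personal identifiers were retained for women who did not consent.
- A woman can be removed from the sample only if she was in it.

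**2. Can the same removal occur in the control arm?** No. Cohorts are formed only at intervention facilities (Study design). For controls, "In the control arm, all eligible women who were willing to participate were consented", and no later removal of this kind is described.

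**3. Does the missing-data rule cover them?** No. Multiple imputation is planned if more than 5% of data are missing, but these women are outside the sample, not missing within it.

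**4. How large could the effect be?** The stated sample sizes serve here only to give arm sizes. They reproduce closely (two-sided 5% level assumed; design effect 2.45; 20% attrition):
- Kenya, 61% v 76%, 85% power: 171 per arm; 171 × 2 × 2.45 / 0.8 = 1,047 (stated 1,026).
- Nigeria, 40% v 55%, 80% power: 173 per arm; 173 × 2 × 2.45 / 0.8 = 1,060 (stated 1,076).

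The planned arm is therefore 1,026 / 2 = 513 in Kenya and 1,076 / 2 = 538 in Nigeria. I treat these as the retained women and add k removed women. With g the difference in facility delivery between retained and removed women:

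fraction removed f = k / (arm + k); shift in the arm's rate = f × g.

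A cancelled cohort has at most 7 women, because eight would have saved it. The values of g are assumed. The value 15 corresponds to removed women delivering at the control rate when group care has the targeted effect.

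| Removed women k | Country | f | g = 10 | g = 15 | g = 30 |
|---|---|---|---|---|---|
| 7 (one cohort) | Kenya | 1.35% | 0.13 | 0.20 | 0.40 |
| 7 | Nigeria | 1.28% | 0.13 | 0.19 | 0.39 |
| 35 (five cohorts) | Kenya | 6.39% | 0.64 | 0.96 | 1.92 |
| 35 | Nigeria | 6.11% | 0.61 | 0.92 | 1.83 |
| 70 (ten cohorts, one per facility) | Kenya | 12.01% | 1.20 | 1.80 | 3.60 |
| 70 | Nigeria | 11.51% | 1.15 | 1.73 | 3.45 |

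Shifts are in percentage points. For a given number of cancelled cohorts and a given g they are upper bounds, because the table assumes full groups of 7 and nobody re-placed. If g is negative, the sign reverses.

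**5. Scale.** With 20% attrition about 410 (Kenya) and 430 (Nigeria) women per arm are analysed. The standard error of the difference is √[2.45 × (0.61×0.39 + 0.76×0.24) / 410] = 5.0 points in Kenya and √[2.45 × (0.40×0.60 + 0.55×0.45) / 430] = 5.3 points in Nigeria. One cancelled cohort is at most 0.40 / 5.0 = 0.08 standard errors; ten could reach 3.60 / 5.0 = 0.72.

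**The case against.** The best defence is that the rule is disclosed and has a reason. Table 2 requires intervention women to be at 20 to 24 weeks at the first group meeting, so a woman who fits no other cohort no longer meets the criteria. The decision comes before that cohort's group care starts and does not depend on her outcome. Facilities were screened on caseload for their ability to form cohorts, so cancellations may have been rare.

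Much of this stands as a limit on size. It does not rescue the label: the ineligibility arises after enrolment, because the cohort did not form, and no control woman can become ineligible in this way.

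Several stronger readings are tempting and are not supported:
- *All women in cancelled cohorts are dropped.* They are first re-evaluated, and only those not re-placed are removed.
- *The trial compares facilities where cohorts formed with all controls.* No facility is dropped. Study design reports four to five cohorts formed per intervention facility and 50 to 54 women enrolled at each facility. The loss is of women within facilities.
- *The effect is necessarily overstated.* If group care works, losing women who did not receive it raises the estimate. But the removed women's own likelihood of facility delivery is unknown and could offset or reverse this.
- *Restoring them would give the effect of adopting the policy.* Intervention-site women who could not attend the first meeting were never consented, and those with no open cohort were sent to individual care.

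**Conclusion.** The point holds in a limited form. The removal rule and the stated intention-to-treat analysis do not fit together, and what would be carried out is a modified intention-to-treat analysis. That conclusion rests on the text alone, plus the strong inference that these women had consented.

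The size is uncertain. The two enrolment flowcharts (Figures 2 and 3) are not shown and may give the count. The text does not say whether the enrolled totals of 1,075 and 1,013 include these women. Under the assumed differences, the distortion is negligible for one or two cancelled cohorts and becomes material only if most facilities had one and few women were re-placed. It should be corrected before results are reported, but it does not by itself undermine the trial.

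**What to change.** Keep every such woman in her randomised arm for both primary outcomes. Recover place of birth and 12-month family planning use through the locator details and phone and home tracing that the article already describes. Participants had to be willing to be followed for up to 12 months after delivery, though whether that still covers women told they had left the study should be confirmed with the ethics committees. Facility records can help with place of birth in Nigeria. They will help less in Kenya, where the Data quality assurance section says deliveries could not be checked this way.

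Recovery may be only partial: Phase 1 data collection is closed in both countries, and Phase 2 is also closed in Nigeria. Where outcomes cannot be obtained:
- call the primary analysis modified intention-to-treat and state the exclusion;
- report, by facility, cohorts cancelled, women re-placed and women removed;
- add a sensitivity analysis that returns the removed women to the denominator over a plausible range of outcomes, for example at control-arm rates.

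Do not simply extend the planned imputation to them. With no outcome from any removed woman, a missing-at-random model would borrow from women who received group care and largely reproduce the problem.

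The cost is limited tracing work, a short change of wording, and possibly a slightly smaller or less precise effect estimate.

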### Sample size

Sample size calculations were done separately for the two countries based on the assumptions that were relevant to the local situation. In each country, the goal was to ensure that the study was adequately powered and each cluster could recruit at least four cohorts.

**Quantitative:** The study is powered to detect a 15 percentage point difference in the primary outcome of interest—proportion of deliveries in a health facility—between the intervention and control arms at the end of Phase 1. For the purpose of sample size calculations, DHS data were used to estimate the average proportions of facility-based delivery in the study regions: 61% for Kenya and 40% for Nasarawa State in Nigeria respectively
^35,
36^.

Intra-class correlation was estimated at 0.03 for both countries, which will lead to a design effect of 2.45, assuming an average of 30 new ANC clients per month in Kenya and 20 new ANC clients per month in Nigeria for each of the 20 health facilities in each country (i.e., 10 facilities per study arm). After factoring an attrition rate of 20%, sample sizes of 1,026 and 1,076 women were determined for Kenya and Nigeria, respectively. The study is powered at 85% for Kenya and 80% for Nigeria to maintain enrollment sufficient for four cohorts per health facility. Three health care providers were recruited per facility (120 total), including only those who routinely provide ANC services.

For Phase 2, we calculated the change in proportion of women who are using a modern FP method at 12 months after birth that would be detectable given the sample size enrolled for Phase 1. Current estimates of PPFP use from the most recent DHS were not available for Kenya or Nigeria. For Kenya, the rate therefore was estimated at 65%, based on rates of PPFP one year after birth in the 2014 endline results from the Kenya Urban Reproductive Health Initiative
^52^. For Nigeria, sample size estimation used the contraceptive prevalence rate (modern methods) of 16% for Nasarawa State from the 2013 Nigeria DHS. Based on assumed 20% attrition in Phase 1 and an additional 20% attrition by the end of Phase 2, the study will be able to detect a 10-percentage point difference in PPFP use at 12 months in Kenya and nine percentage point difference in Nigeria between study arms.

**Qualitative:** Approximately 15 IDIs and six focus group discussions (FGDs) will be conducted per phase in each country. In sampling for both IDIs and FGDs, the aim is to draw a sample reflective of the full range of responses to the G-ANC intervention model. For Phase 1, the IDIs and FGDs were conducted with women and health care providers both near and far from district referral hospitals to capture variation in challenges related to training, logistics, supervision, transport, and care seeking based on location.

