The study will be conducted in two phases. The primary outcome of Phase 1 is an increase in the percentage of women who have a facility-based delivery. In Phase 1, the study will test whether re-organization of care from individual ANC to G-ANC, and the corresponding emphasis on participatory care and learning, will: improve the provision and experience of ANC; empower women and health care providers; and increase health literacy—together, leading to greater practice of healthy behaviors and health service utilization among women experiencing group care. The primary outcome for Phase 2 is an increase in the use of a modern family planning (FP) method at one year after birth. In Phase 2, the study will test whether women who remain in the same cohorts and receive care in groups for the first year postpartum report improved practice of health, hygiene, and early childhood development behaviors and increased health service utilization. Outcomes are measured at the individual participant level.

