### Study status

Enrollment of study participants and collection of baseline data began in October 2016, with the first group meetings occurring at the end of the month. Enrollment was completed in January 2017 in Nigeria and June 2017 in Kenya. Overall 1,075 and 1,013 pregnant women were enrolled in Nigeria and Kenya, respectively.
Figure 2 and
Figure 3 show the enrollment cascade for the two countries.

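### The Phase 2 detectable differences (10 points in Kenya, 9 in Nigeria) do not follow from the protocol's own ICC of 0.03; they match a calculation without clustering

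*Protocol article*

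**What the plan says.** All the inputs are in the Sample size section of the protocol article. The Phase 1 paragraph gives the clustering assumption: "Intra-class correlation was estimated at 0.03 for both countries, which will lead to a design effect of 2.45". It also gives 20 facilities per country (10 per arm), 20% attrition, and the totals: "sample sizes of 1,026 and 1,076 women were determined for Kenya and Nigeria, respectively". Stated power is 85% for Kenya and 80% for Nigeria, for a 15-point difference in facility delivery.

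The next paragraph works out what Phase 2 can detect from the sample already fixed by Phase 1. The baseline rates are: "For Kenya, the rate therefore was estimated at 65%, based on rates of PPFP one year after birth"; and for Nigeria, "sample size estimation used the contraceptive prevalence rate (modern methods) of 16% for Nasarawa State". Attrition compounds: "Based on assumed 20% attrition in Phase 1 and an additional 20% attrition by the end of Phase 2". The result is "the study will be able to detect a 10-percentage point difference in PPFP use at 12 months in Kenya and nine percentage point difference", the second figure being Nigeria's. This paragraph gives no ICC, design effect, significance level, sidedness or power.

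The Background defines the outcome directionally: "The primary outcome for Phase 2 is an increase in the use of a modern family planning (FP) method at one year after birth".

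**The concern.** Phase 2 follows the same women in the same randomized facilities, and the Abstract says that the primary outcome analyses will account for clustering. A detectable difference for Phase 2 should therefore carry a design effect, as Phase 1 does. Phase 1 needs a 15-point difference with 20% attrition. Phase 2 has fewer women left, yet claims 9 to 10 points. A baseline further from 50% explains part of that in Nigeria. It explains almost none of it in Kenya, where the baseline moves only from 61% to 65%.

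At stake is a stated design property of a primary outcome. If the figures ignore clustering, readers are told that gains of 10 and 9 points can be detected when the trial would miss gains of that size close to half the time under its own ICC.

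**Working it through.** **Method.** Two-proportion normal approximation, unpooled variance, two-sided 5%:

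SE = √{[p₁(1−p₁) + p₂(1−p₂)] × DE / n}, power = Φ(d/SE − 1.96), with n women per arm.

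The article does not state alpha or sidedness, so two-sided 5% is an assumption. Phase 1 tests it.

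**Step 1: reproduce Phase 1 (DE 2.45, 80% retained, 15 points).**
- Kenya: n = 1,026 × 0.8 / 2 = 410.4; 61% v 76%; SE = √(0.4203 × 2.45 / 410.4) = 0.0501; power = Φ(2.995 − 1.96) = 85.0%. Stated: 85%.
- Nigeria: n = 1,076 × 0.8 / 2 = 430.4; 40% v 55%; SE = √(0.4875 × 2.45 / 430.4) = 0.0527; power = Φ(2.847 − 1.96) = 81.3%. Stated: 80%.

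Without the design effect both would exceed 99%, so Phase 1 did include it, and the method is close to the one used.

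**Step 2: Phase 2 sample.** Retention is 0.8 × 0.8 = 0.64.
- Kenya: 1,026 × 0.64 / 2 = 328.3 per arm, 32.8 per facility.
- Nigeria: 1,076 × 0.64 / 2 = 344.3 per arm, 34.4 per facility.

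**Step 3: Phase 2 with no design effect (DE = 1).**
- Kenya, 65% v 75%: SE = √(0.4150 / 328.3) = 0.0356; power = Φ(2.813 − 1.96) = 80.3%; detectable difference at 80% power 10.0 points. Stated: 10.
- Nigeria, 16% v 25%: SE = √(0.3219 / 344.3) = 0.0306; power = Φ(2.943 − 1.96) = 83.7%; detectable difference 8.5 points. Stated: 9.

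**Step 4: Phase 2 with ICC 0.03.** DE = 1 + (m − 1) × 0.03, where m is retained women per facility.
- Kenya: DE = 1 + 31.8 × 0.03 = 1.95; SE = 0.0497; power = Φ(2.012 − 1.96) = 52%.
- Nigeria: DE = 1 + 33.4 × 0.03 = 2.00; SE = 0.0433; power = Φ(2.080 − 1.96) = 55%.

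Solving for the difference that gives 80% power:

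| Phase 2 assumption | Kenya: power at 10 points | Kenya: detectable, 80% power | Nigeria: power at 9 points | Nigeria: detectable, 80% power |
|---|---|---|---|---|
| No design effect | 80% | 10.0 | 84% | 8.5 |
| ICC 0.01 | 69% | 11.3 | 72% | 10.0 |
| ICC 0.03 | 52% | 13.6 | 55% | 12.4 |
| ICC 0.03, t on 18 df | 48% | 14.3 | 50% | 13.2 |
| ICC 0.05 | 42% | 15.4 | 44% | 14.5 |

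**Step 5: sensitivity.** Pooled variance at ICC 0.03 gives 51.6% and 54.3%. Keeping DE at 2.45 instead of letting it shrink with attrition gives 44% and 47%. Reading the attrition as additive (60% retained) gives about 51% and 53%. Actual enrolment ("Overall 1,075 and 1,013 pregnant women were enrolled in Nigeria and Kenya, respectively") leaves 52% and 55%. With no attrition at all, power is still only 60% and 63%. For 80% power at the stated differences, the ICC would have to be about 0 in Kenya and about 0.003 in Nigeria.

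**The case against.** The strongest reply is that the article does not show how the Phase 2 figures were obtained, so the diagnosis goes beyond the text. Four parts of that deserve an answer.

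- **Omission as fact.** A reader might infer that the article admits to, or proves, leaving out the design effect. It does neither. The unclustered calculation fits Kenya closely, but Nigeria's 8.5 reaches 9 only by rounding. Other routes exist: a one-sided 5% test with ICC 0.01 gives 10.1 and 8.8 points with clustering included, and the directional wording of the outcome makes one-sidedness conceivable. However, that route needs an ICC that the article does not state and a sidedness that Phase 1 does not suggest. With ICC 0.03, one-sided power is still only 64% and 67%.
- **Phase 2 power.** A reader might infer that 80% is claimed for Phase 2. The 85% and 80% stand in the Phase 1 paragraph, and the Phase 2 sentence names no power. The fault lies in the detectable differences, not in a stated Phase 2 power.
- **The ICC.** The 0.03 is given for facility delivery and is not restated for family planning. Pair-matching (which included availability of family planning services) and covariate adjustment could also reduce between-facility variance, by an amount the article does not give. This stands, and it is why power is given as a range. It does not rescue the figures: ICC 0.01 gives 69% and 72%, and in Kenya essentially all between-facility variance would have to vanish.
- **Consequences.** The planned analysis accounts for clustering, so estimates and intervals are unaffected. This also stands. The error is in what the design is said to detect.

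**Conclusion.** The Phase 2 sentence is wrong as written. Detectable differences of 10 and 9 points do not follow from ICC 0.03, 10 facilities per arm and the stated attrition at two-sided 5% and 80% power. They match an unclustered calculation closely enough that the design effect was very likely omitted, but that cause is inferred.

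Under ICC 0.03 the trial has roughly even odds of detecting the stated gains: about 52% and 55% by the normal approximation, or 48% and 50% with t on 18 df. The stated differences are too small by about 3.6 points in Kenya (13.6 − 10) and 3.4 in Nigeria (12.4 − 9). The conclusion rests on two-sided 5% (unstated, but supported by the Phase 1 reproduction), on 64% retention, and on carrying the ICC over to family planning. The exact power moves with the ICC; the failure to reach 80% does not, for any ICC from 0.01 to 0.05. The finding does not imply that the planned analysis is invalid.

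**What to change.** Replace the Phase 2 sentence with one that includes the design effect and names the ICC, retention, alpha, sidedness, power and method. At ICC 0.03, 64% retention, two-sided 5% and 80% power, it would give about 13.6 points (Kenya) and 12.4 points (Nigeria) by the normal approximation, or 14.3 and 13.2 with t on 18 df. One method should be used for both countries. Say that the ICC is carried over from facility delivery, and show the range for ICC 0.01 to 0.05: about 11.3 to 15.4 points in Kenya and 10.0 to 14.5 in Nigeria, by the normal approximation.

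If the original figures used a different ICC, a one-sided test or a different power, state that instead, so that they can be reproduced.

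The cost is a less favourable stated figure. No participants are added, and neither the conduct of the trial nor the planned analysis changes.
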